### Statistical analysis

The statistical significance level will be set at 5%, and the data will be analyzed using intention-to-treat and per protocol approaches. Data will be processed with the last observation carried forward method for the intention-to-treat analysis, and will be performed using IBM SPSS Win ver. 19.0 statistical software (IBM Co., Armonk, NY, USA).

All demographic and clinical characteristics of the subjects (such as sex, age, and weight) will be processed based on descriptive analyses. Quantitative data will be presented as average, standard deviation, median value, and range. Qualitative data will be presented as the frequency and percentage. The study will identify the comparative equivalence of demographic variables and clinical characteristics between the experimental and control groups.

In order to identify differences in VAS, PainVision scores, SF-MPQ and ODI scores between the experimental and control group based on time (baseline, weeks one, three and five), a repeated-measure twofactor analysis will be performed to identify differences between groups, differences within each group based on time, and the effects of the interaction of the variables based on group. If the interaction between group and time is statistically significant, the point at which the pattern of results between the two groups changes will be checked.

The Chi-square test will be used to compare groups and the incidence frequency of adverse events related to acupuncture and interlaminar epidural steroid injection.

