### Hypotheses

In this randomized controlled two-arm clinical trial, we will evaluate the effect of acupuncture as an adjunct therapy to spondylolisthesis. The primary hypothesis is that acupuncture treatment in addition to interlaminar epidural steroid injection reduces pain (as measured by VAS) significantly more than interlaminar epidural steroid injection only. The secondary hypotheses are that: the score of the PainVision system (PS-2100, Nipro Corporation, Osaka, Japan), is significantly lower in the experimental group than that in the control group; additional acupuncture treatment reduces the score on the short-form McGill Pain Questionnaire (SF-MPQ) significantly more than interlaminar epidural steroid injection alone; interlaminar epidural steroid injection combined with acupuncture is significantly better than interlaminar epidural steroid injection alone in reducing the score on the Oswestry Disability Index (ODI).

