## Methods/Design

### Design

The study is a randomized controlled pilot clinical trial. It is designed to assess the efficacy and safety of acupuncture treatment in patients with low back pain due to low-grade spondylolisthesis. The protocols used adhere to the principles of the Declaration of Helsinki and have been approved by the institutional review board of Daegu Catholic University Hospital (IORG0004453), where the study will take place. The trial is registered with the US National Institutes of Health Clinical Trials registry. Written consent will be obtained from each participant before any treatment is given.

The outcome assessment and statistical analyses will be performed by professionals blinded to the assignment of patients. The trial process is presented in Figure 
1. The trial will run for five weeks. Patients will be allocated to two groups; the control group will only receive three interlaminar epidural steroid injections and the experimental group will receive all three steroid injections as well as nine acupuncture sessions (three sessions a week forthree weeks). Assessments will be made at baseline, and again at one, three and five weeks thereafter. The week five assessment will be performed two weeks after treatment cessation.

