### Participants

One of the main objectives of this study is to provide an estimate of the sample size required for the full-scale randomized controlled clinical trial. We plan to recruit 14 patients into this pilot study. A target of 14 patients with spondylolisthesis has been set.

The inclusion criteria are that participants must: be aged 18 to 65 years, have Meyerding Grade I to II spondylolisthesis, have low back pain of at least one-year duration, be available for possible follow-up during the clinical trial, and provide written informed consent voluntarily.

The exclusion criteria are: cauda equina syndrome, persistently exacerbated symptoms, progressive neurologic signs (sensory or motor changes); previous spine surgery; senile dementia, impaired cognitive function or other cerebral disease, severe psychiatric or psychological disorders; severe, concomitant disease (neuromuscular scoliosis, neurodegenerative disease); all contraindications to corticosteroid injection (e.g., insulin-dependent diabetes); alcohol/drug abuse; significant renal or hepatic disease; pregnant, lactating or planning a pregnancy; hypersensitive reaction to acupuncture treatment; inability to comprehend or express oneself in the Korean language; an individual deemed to be ineligible by a physician; or refusal to participate in the trial or to provide informed consent.

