### Primary outcome measurement

#### VAS

Pain intensity will be assessed using a10 cm VAS of subjective pain assessment. Each patient will rate their pain on a scale of 0 to 10 (0 being an absence of pain and 10 being the worst pain imaginable)
[18,19]. VAS measurements will be made at baseline, and at one, three and five weeks. Our primary end point is three-week VAS.

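### Last observation carried forward is the only missing-data method for the intention-to-treat analysis; if patients leave before week 3, it biases the primary VAS comparison

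*Protocol article*

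**What the plan says.** In the protocol article, the Statistical analysis section says that "the data will be analyzed using intention-to-treat and per protocol approaches". For the first of these it fixes the handling of missing scores: "Data will be processed with the last observation carried forward method for the intention-to-treat analysis". It names no other method for missing data. The main comparison is a two-factor repeated-measures analysis of group, time and their interaction.

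The section on the VAS says "Our primary end point is three-week VAS" and "VAS measurements will be made at baseline, and at one, three and five weeks". On week 5, the Design section adds: "The week five assessment will be performed two weeks after treatment cessation".

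The Background section anticipates possible short-term benefit from epidural steroid injections, which both arms receive. The Hypotheses section puts its main efficacy claim this way: "acupuncture treatment in addition to interlaminar epidural steroid injection reduces pain (as measured by VAS) significantly more than interlaminar epidural steroid injection only". Under Withdrawal and dropout, participation ends on refusal, withdrawal of consent or protocol violation. The Participants section says "We plan to recruit 14 patients into this pilot study". No dropout rate, VAS trajectory, standard deviation or allocation ratio is given.

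**The concern.** Carrying the last score forward assumes that a patient's pain would have stayed where it was last recorded. The trial is built on the opposite expectation: scores should fall during the three treatment weeks, and fall further with acupuncture. A missing week-3 score can only be replaced by a baseline or week-1 score, and on the trial's own premise that is probably too high. The error is larger in the arm that improves more and in the arm that loses more patients, so it does not cancel between arms in general.

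At stake is the estimated week-3 difference, both as the test of the stated efficacy hypothesis and as information for the full-scale trial. If each arm has 7 patients, one dropout is 1/7, or about 14%, of an arm.

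A lesser issue arises at week 5, a secondary time point. There the method fills an off-treatment visit with a score from the treatment period, so any return of pain after treatment stops is not reflected for that patient.

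**Working it through.** The plan contains no figure to reproduce, so the check is of the method's expected result.

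**Inputs from the protocol article**
- Primary end point: VAS at week 3.
- Earlier scores: baseline and week 1 only.
- Total sample: 14.
- Expected direction: pain falls, and falls more in the experimental arm.

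**Assumptions**
- 7 patients per arm.
- Mean VAS at weeks 0, 1 and 3 of 6, 5, 3 (experimental) and 6, 5.3, 4 (control).
- Dropout unrelated to the patient's scores.

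**Formula.** Let D be the true week-3 difference, control minus experimental. Let dE and dC be the dropout shares, and gE and gC the mean fall from the carried score to week 3 in each arm. The expected difference after carrying forward is

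D + dC × gC − dE × gE.

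Here D = 4 − 3 = 1.0. If week 1 is carried, gE = 5 − 3 = 2 and gC = 5.3 − 4 = 1.3. If baseline is carried, gE = 6 − 3 = 3 and gC = 6 − 4 = 2.

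**Worked cases, week 1 carried**
- Two experimental dropouts: 1 − (2/7) × 2 = 0.43.
- Two control dropouts: 1 + (2/7) × 1.3 = 1.37.
- Two in each arm: 1 + (2/7) × (1.3 − 2) = 0.80.

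| Dropouts of 7 (experimental, control) | Week 1 carried | Baseline carried |
|---|---|---|
| 0, 0 | 1.00 | 1.00 |
| 1, 0 | 0.71 | 0.57 |
| 0, 1 | 1.19 | 1.29 |
| 1, 1 | 0.90 | 0.86 |
| 2, 0 | 0.43 | 0.14 |
| 0, 2 | 1.37 | 1.57 |
| 2, 2 | 0.80 | 0.71 |

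**Direction.** With equal dropout d, the bias is d × (gC − gE). It is zero if the arms fall equally, and points towards no effect if the experimental arm falls more. With unequal dropout the sign depends on which of dE × gE and dC × gC is larger.

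**Second set of assumed means.** Take 6.5, 5.0, 3.5 (experimental) and 6.5, 5.5, 4.5 (control), again with D = 1.0. With week 1 carried, gE = 1.5 and gC = 1.0. The results are 1 − (2/7) × 1.5 = 0.57, 1 + (2/7) × 1.0 = 1.29 and 1 + (2/7) × (1.0 − 1.5) = 0.86. In a simulation of 20,000 runs with these means (SD 2, correlation 0.6, random dropout after week 1), the observed week-3 scores alone gave 0.99 to 1.01. Under those conditions the bias comes from carrying forward, not from the dropout.

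**No true effect.** If both arms follow 6.5, 5.5, 4.5, equal dropout gives no bias. Two dropouts in one arm give (2/7) × 1.0 = 0.29 with week 1 carried, or (2/7) × 2.0 = 0.57 with baseline carried, against the arm that lost them.

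**Week 5.** Suppose means move from 3.5 to 4.25 (experimental) and from 4.5 to 4.75 (control) between weeks 3 and 5, and 1 of 7 in each arm leaves after week 3. The true week-5 difference is 4.75 − 4.25 = 0.50. Carrying forward gives (6/7 × 4.75 + 1/7 × 4.5) − (6/7 × 4.25 + 1/7 × 3.5) = 0.57.

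**The case against.** The strongest reply is that this is a 14-patient pilot whose stated primary aim is feasibility and safety. It cannot settle efficacy whatever is done about missing scores. Treatment is short, patients must be available for follow-up to be included, and dropout may be small. In a simulation with no true effect (SD 2, correlation 0.6, means 6, 5, 3.5, week 1 carried, week-3 ANCOVA), the sampling SD of the estimate was about 0.9. The root-mean-square error of carrying forward was close to that of a complete-case analysis: 0.92 against 0.94 with one dropout in one arm, and 1.00 against 0.99 with two. A per protocol analysis is also planned, so a disagreement between the two would be visible.

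Much of this stands, and it lowers the severity. It does not remove the point. The article still states an efficacy hypothesis and a primary end point, and the bias is avoidable. The per protocol analysis is no remedy, because it selects patients by what happens after randomization.

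Four stronger readings are tempting and are not supported:

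- **A seriously inflated false-positive rate.** In the simulation just described, rejection was 4.7% with one dropout against none, 5.9% with two against none and 8.4% with three against none. With two in each arm it was 3.5%. Only heavy, one-sided loss matters, and these rates belong to a week-3 ANCOVA, not to the repeated-measures analysis planned.
- **A distorted SD for planning the full trial.** With week 1 carried, the SD rose from 2.00 to only about 2.03 to 2.16, which is small beside the uncertainty of any SD from 14 patients.
- **Dropout that will be unbalanced.** Nine extra sessions could cost patients in one arm, and disappointment could cost them in the other. The article gives no rate for either.
- **Arms that are known to improve.** That is the article's expectation, not a result.

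**Conclusion.** The point holds conditionally. If patients are lost before week 3 and pain falls as the article expects, the planned intention-to-treat analysis biases the primary comparison. Unequal dropout can move the difference either way. Equal dropout moves it towards no effect if the experimental arm improves faster. With no dropout there is no bias, and with equal dropout and identical trajectories there is none either.

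The size is illustrative only. For a true difference of 1.0, the assumed means give 0.43 to 1.37 with two week-1 dropouts in one arm, and about 0.8 with two in each. The means, the dropout numbers and 7 per arm are all assumptions. The week-5 issue is secondary. For a pilot of this size the change should be made, but the trial does not stand or fall by it.

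**What to change.** For the intention-to-treat analysis, replace last observation carried forward with a likelihood-based mixed model for repeated measures on all observed post-baseline VAS scores. Include baseline VAS, group, week and group by week, and use small-sample degrees of freedom. Name the week-3 group contrast as the primary estimate. Keep carrying forward, if wanted, only as a labelled sensitivity analysis. A patient with no post-baseline score adds nothing to this model, so report the number of such patients by arm.

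The cost is a change of analysis wording and slightly more analysis work, with no new data or visits. The article describes the trial as still recruiting, so the change can precede the analysis. The model relies on scores being missing at random given those observed. An additional analysis that shifts the missing scores by a stated amount would probe that assumption, but is optional at this sample size.

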**Methods/Design:**

The study is a randomized controlled pilot clinical trial of five weeks duration. Fourteen patients will be recruited and randomly allocated to two groups: an acupuncture plus interlaminar epidural steroid injection group (experimental group), and an interlaminar epidural steroid injection group (control group). All patients will be administered an interlaminar epidural steroid injection once a week for three weeks (three injections in total), but only the experimental group will receive additional treatment with three acupuncture sessions a week for three weeks (nine acupuncture sessions in total). The primary outcome will be measured by the visual analogue scale (VAS). Our primary end point is three-week VAS. The secondary outcome will be measured using the PainVision system, the short-form McGill Pain Questionnaire, and the Oswestry Disability Index. Assessments will be made at baseline and at one, three and five weeks thereafter (that is, the five-week assessment will be made two weeks after treatment cessation).

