### Randomization

Patients will be randomized using a computerized random number generator by an independent statistician blinded to patient assignment. Block randomization will be performed once a participant is confirmed to be eligible and their written informed consent has been obtained.

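### Fourteen patients cannot show baseline equivalence, and the stated repeated-measures model handles baseline VAS poorly; an ANCOVA of week-3 VAS on baseline VAS would serve the primary end point better

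*Protocol article*

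**What the plan says.** The protocol article fixes the size of the study under Participants: "We plan to recruit 14 patients into this pilot study". Its abstract adds the number of arms: "Fourteen patients will be recruited and randomly allocated to two groups". The Randomization section specifies blocks but gives no allocation ratio and no stratification factor.

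Under Primary outcome measurement the target is explicit: "Our primary end point is three-week VAS".

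The Statistical analysis section first says of baseline data: "All demographic and clinical characteristics of the subjects (such as sex, age, and weight) will be processed based on descriptive analyses". The same paragraph ends with a further commitment: "The study will identify the comparative equivalence of demographic variables and clinical characteristics between the experimental and control groups". It gives no margin, no test and no rule for acting on the result.

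For efficacy, "a repeated-measure twofactor analysis will be performed to identify differences between groups". The same analysis also covers change over time and the group-by-time interaction. The time factor has four levels: baseline and weeks one, three and five. Baseline VAS is thus one of the repeated outcomes. The same holds for PainVision, SF-MPQ and ODI.

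**The concern.** Two things in the stated plan work badly together.

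First, the baseline sentence promises a conclusion, equivalence, that so small a trial cannot reach. After proper randomization any baseline difference is due to chance. The useful question is how large the difference is and how the analysis deals with it.

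Second, the stated model deals with it poorly. With the pre-treatment visit as a level of time, the group main effect includes a measurement that treatment cannot have influenced. The interaction compares change from baseline. A chance difference in starting pain pushes these two terms in opposite directions, and neither is a direct test of VAS at week 3.

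At stake is the reading of the one efficacy contrast the trial names as primary. The Participants section says that a main objective is to inform the sample size of the full-scale trial, so a group difference distorted by starting pain could carry over into that planning.

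**Working it through.** **Inputs.** From the article: 14 patients, two groups, four assessment times, week-3 VAS as primary end point. The article gives no power calculation, so there is no figure to reproduce. Assumed: 7 v 7 allocation (6 v 8 and 5 v 9 as a range); equal SDs at all visits; the same correlation ρ between baseline and each later visit, from 0.3 to 0.7. Results are in SD units because no SD is given.

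**1. Can equivalence be shown?**
- Standard error of a mean difference: √(2/7) = 0.535 SD, with 12 degrees of freedom.
- 90% CI half-width: 1.782 × 0.535 = 0.95 SD. For 6 v 8: 1.782 × √(1/6 + 1/8) = 0.96 SD. For 5 v 9: 1.782 × √(1/5 + 1/9) = 0.99 SD.
- Chance of concluding equivalence by two one-sided tests when the groups truly do not differ (400,000 simulated trials, 7 v 7): 0.05% at a margin of 0.5 SD, 4% at 0.8 SD, 17% at 1.0 SD and 68% at 1.5 SD. The last margin is too wide to mean comparable.
- Patients per arm for 80% power, 2 × ((1.645 + 1.282)/margin)²: about 69 at 0.5 SD, 27 at 0.8 SD and 18 at 1.0 SD.

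**2. How often does a sizeable imbalance arise?** For any one continuous variable, the chance of a difference of at least 0.5 SD is 2 × (1 − Φ(0.5/0.535)) = 0.35, or about one randomization in three.

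**3. What does the stated model do with it?** Let d = 0.5 SD be the baseline VAS difference. With no treatment effect, the expected difference at each later visit is ρd.
- Group main effect, averaged over four visits: d(1 + 3ρ)/4.
- Change contrast, week 3 minus baseline: ρd − d = −d(1 − ρ).

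| ρ | Main effect | Change contrast | ANCOVA at week 3 |
|---|---|---|---|
| 0.3 | +0.24 | −0.35 | 0 |
| 0.5 | +0.31 | −0.25 | 0 |
| 0.7 | +0.39 | −0.15 | 0 |

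ANCOVA subtracts the expected carry-over ρd, which leaves zero when the relation is linear. The main effect is also diluted: a constant treatment effect δ at the three later visits appears as (0 + 3δ)/4 = 0.75δ.

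**4. Does ANCOVA pay its way at this size?** Variances below are relative to an unadjusted week-3 difference.
- Change contrast: 2(1 − ρ) = 1.40, 1.00 and 0.60 for ρ = 0.3, 0.5 and 0.7.
- ANCOVA: (1 − ρ²) × (1 + 1/10) = 1.00, 0.83 and 0.56. The factor 1 + 1/10 is the average price of estimating the slope with 12 within-group degrees of freedom.

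ANCOVA has the smaller variance of the two across the whole range.

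**The case against.** The strongest reply is that one loosely worded sentence is being made to carry too much. It closes a paragraph about descriptive summaries and may mean only that the groups will be checked for comparability. Nothing later in the section depends on it.

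Much of that stands. A reader might infer that chance imbalance would be declared absent after a non-significant test. The article names no baseline test, margin or decision rule, so neither that inference nor any rate of false equivalence claims built on it is supported. A reader might also infer that the equivalence statement is the only protection against imbalance. It is not: the interaction term takes partial account of baseline outcome values by comparing change, though it does not do what ANCOVA does and does not cover demographic factors.

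It is also fair to say that chance imbalance does not invalidate a randomized test. Averaged over all randomizations the shifts above cancel, and they are already reflected in the standard error. They matter conditionally, in the one trial that is run. The missing mention of covariates is no fault in itself, since a condensed article may leave that to a fuller document.

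What the objection does not remove is the model that the article does state, with baseline as a level of time, and its mismatch with a week-3 end point.

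**Conclusion.** The point holds in a limited form. The equivalence wording promises what 14 patients cannot show, and this is insensitive to the assumed split (90% half-width 0.95 to 0.99 SD). Correcting that wording alone would change little.

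The more useful part concerns the model. A 0.5 SD baseline imbalance moves its two group-related terms in opposite directions, by 0.24 to 0.39 SD and by 0.15 to 0.35 SD, and neither term is a direct test of the primary end point. These sizes rest on the assumed correlation range, equal SDs and a common correlation across visits.

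The documents do not support the stronger reading that the trial will report a false finding of comparability, or that its planned test is invalid. Nor should the shifts be read as the bias of a stand-alone unadjusted week-3 comparison, because the article describes no such test. The stakes are moderate: the stated primary aim is feasibility and safety, but the article also states an efficacy hypothesis on VAS.

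**What to change.** - Replace the equivalence sentence with a statement that baseline characteristics will be described by arm, with no claim of equivalence.
- Make the primary analysis an ANCOVA of week-3 VAS on group, with baseline VAS as a covariate. Prespecify it and apply it whatever imbalance is observed.
- If the repeated-measures model is kept, use weeks one, three and five as outcomes with baseline as a covariate, and take the group difference at week 3 as the primary estimate.
- Treat PainVision, SF-MPQ and ODI in the same way.

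The cost is a few sentences in the Statistical analysis section and one degree of freedom per model (12 to 11 residual degrees of freedom for the week-3 ANCOVA with 14 patients). All the data needed are already in the assessment schedule.

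### The primary endpoint is week-3 VAS, but the only planned efficacy analysis does not assure a between-group comparison at week 3

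*Protocol article*

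**What the plan says.** The section on the primary outcome is explicit: "Our primary end point is three-week VAS". The abstract repeats it. The Hypotheses section names no week; it says that added acupuncture "reduces pain (as measured by VAS) significantly more than interlaminar epidural steroid injection only".

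For VAS and the three secondary scores alike, the Statistical analysis section seeks differences "between the experimental and control group based on time (baseline, weeks one, three and five"). The method is "a repeated-measure twofactor analysis will be performed to identify differences between groups, differences within each group based on time", together with the group-by-time interaction. Baseline is thus one of four levels of the outcome. The section then says that "If the interaction between group and time is statistically significant, the point at which the pattern of results between the two groups changes" is to be examined. The significance level is 5%. The only other test named there, the chi-square test, is for adverse events.

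On size and purpose: "We plan to recruit 14 patients into this pilot study". The Background gives feasibility and safety as the primary aim, and the Participants section makes an estimate of the full trial's sample size a main objective.

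**The concern.** A declared primary endpoint should have an analysis that always estimates it. Here the endpoint is one time point, while the analysis delivers tests over four. The group main effect is a different quantity from the week-3 difference. The interaction test is global. The step that looks at single weeks depends on the interaction and is aimed at the place where the pattern changes, not at week 3. The trial could follow its plan fully and report no between-group estimate or test of its primary endpoint. That matters for planning too, because the week-3 difference and its variability are what a full trial with the same endpoint would be sized on.

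**Working it through.** The protocol states no power, effect size or SD, so there is no figure to reproduce. The mismatch follows from the text; the numbers only show its possible size.

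**Inputs from the protocol:** 14 patients, two groups, four time levels, 5% level.

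**Assumptions:** 7 per arm (ratio not stated), two-sided tests, SD 1 at every visit, equal correlation ρ between visits, no missing data, true difference 1 SD at week 3 and zero at baseline. Main pattern d = (0, 0.5, 1, 0.5) at baseline and weeks 1, 3 and 5.

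**Step 1. What the group main effect estimates.** Its expectation is the mean of the four differences. As a share of the week-3 difference:

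| Pattern (weeks 0, 1, 3, 5) | Share |
|---|---|
| 0, 1, 1, 1 | 3/4 = 0.75 |
| 0, 0.5, 1, 1 | 2.5/4 = 0.625 |
| 0, 0.5, 1, 0.5 | 2/4 = 0.5 |
| 0, 0, 1, 0 | 1/4 = 0.25 |

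**Step 2. Group test, main pattern.** The variance of a patient's four-visit mean is v = (1 + 3ρ)/4. Noncentrality is 0.5² / (2v/7), with F on 1 and 12 df.
- ρ = 0.5: v = 0.625, noncentrality 1.40, power 19%.
- ρ = 0.7: v = 0.775, noncentrality 1.13, power about 17%.

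**Step 3. Interaction test, main pattern.** Noncentrality is (7/2) × Σ(d − mean d)² / (1 − ρ), with F on 3 and 36 df. Here Σ(d − mean d)² = 0.25 + 0 + 0.25 + 0 = 0.5.
- ρ = 0.5: 3.5 × 0.5 / 0.5 = 3.50, power 29%.
- ρ = 0.7: 3.5 × 0.5 / 0.3 = 5.83, power 46%.

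**Step 4. Week-3 comparison with and without the condition** (simulation, 20,000 trials per setting; the same baseline-adjusted ANCOVA in both rows).

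| | ρ = 0.5 | ρ = 0.7 |
|---|---|---|
| Week-3 ANCOVA, always done | 47% | 63% |
| Week-3 ANCOVA, only after a significant interaction | 24% | 41% |
| Share of significant ANCOVA results lost to the condition | 1 − 0.236/0.474 = 50% | 1 − 0.406/0.625 = 35% |

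**Step 5. How far this depends on the assumptions.** Across the four patterns and ρ = 0.3, 0.5 and 0.7, with 1 SD at week 3, the interaction is significant in 21% to 65% of trials, so single weeks go unexamined in 35% to 79%. With 1.5 SD they go unexamined in 4% to 55%. With equal effects at all post-baseline weeks, the interaction test has 42% (ρ = 0.5) and 65% (ρ = 0.7) power, against 47% and 63% for the unconditional ANCOVA. The interaction test is therefore not always the weaker one.

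**The case against.** Four points can be made for the plan.

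- **It is a feasibility pilot.** With 14 patients any efficacy test is weak, and the primary aim is not efficacy. This stands and lowers the severity. It does not remove the point: the protocol states a primary efficacy hypothesis with a 5% level and wants sample-size information for the full trial.
- **The hypothesis is tested.** A reader might infer that the primary hypothesis may never be tested at all. The document does not support that. The hypothesis names no week, the interaction test is always run, and with baseline as a level it asks whether change over time differs between arms. What is not assured is the declared week-3 comparison. A significant 3-df interaction does not show which arm did better at week 3, or by how much.
- **Type I error.** A reader might infer that two routes to success double the error rate. If either omnibus test counted, the rate would be about 1 − 0.95² = 9.75%. The protocol states no such rule; it leaves open which effect decides. The figure is conditional on a rule that the reader would have to supply.
- **Baseline as a repeated level is not invalid.** This is correct, since the interaction then carries the comparison of change. Adjusting for baseline is the more direct way to estimate the week-3 difference, but the fault is the missing week-3 contrast, not the use of baseline as a level.

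Descriptive means and SDs are also promised, so a raw week-3 difference could probably be worked out. It would come without a planned between-group estimate or interval.

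**Conclusion.** The point holds as a mismatch between endpoint and analysis. It is not an omission that an unseen analysis plan would excuse, because the article itself states the model, its time levels and the condition for looking at single weeks.

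The size depends on an assumed SD structure, correlation, effect pattern and 7:7 split. In the main illustration, making the week-3 comparison conditional cuts its power from 47% to 24% at correlation 0.5, and from 63% to 41% at 0.7. These figures should not be read as a general claim that the plan is underpowered relative to ANCOVA. The dilution of the group main effect needs only a zero expected baseline difference and the assumed pattern. In a 14-patient feasibility pilot this should be fixed; it does not invalidate the trial.

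**What to change.** Name one primary efficacy analysis: the between-group difference in week-3 VAS adjusted for baseline VAS, with its 95% CI. Use ANCOVA, or the week-3 contrast from a mixed model for weeks 1, 3 and 5 with baseline VAS as covariate. State that it is reported whatever the interaction test shows. Make the repeated-measures group and interaction tests, and the week-1 and week-5 contrasts, secondary.

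The cost is a rewording of the analysis section and one degree of freedom for the covariate (11 residual df instead of 12 for a week-3 comparison of 14 patients). No new data are needed, since VAS is already scheduled at baseline and week 3. The change should be made before the data are analysed.
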